#### **5.5 Laboratory Data**

All laboratory results such as plasma somatostatin concentration, plasma glucagon concentration, Haemoglobin, white cell count, haematocrit and platelets etc. will be reviewed and the reports signed by a qualified member of the clinical research team, who will record in the CRF whether it is normal, abnormal but not clinically significant, or abnormal and clinically significant.

The Freestyle Libre data will be collected, stored and retrieved in accordance with the privacy policy of Freestyle Libre web site controlled by Abbott Laboratories. The cloud-based diabetes management system has been assessed and approved by the University of Oxford Information Security Team.

### **6 Data Handling Conventions**

#### **6.1 Data Monitoring**

Regular monitoring will be performed according to the trial specific Monitoring Plan. Data will be evaluated for compliance with the protocol and accuracy in relation to source documents as these are defined in the trial specific Monitoring Plan. Following written standard operating procedures, the monitors will verify that the clinical trial is conducted and data are generated, documented and reported in compliance with the protocol, GCP and the applicable regulatory requirements.

## 6.2 Data Transformations

No data transformations have been identified in this SAP.

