### **1.3.4 Sample Size Determination**

There are currently no data on plasma glucagon levels from human trials using low-dose sulfonylureas in patients with type 1 diabetes. The sample size calculations are based on the data generated from the LEGEND-A trial [4] (NCT02830048 - completed) and interim analysis from the DEPTH trial (NCT03537131 – suspended due to the COVID-19 pandemic).

The LEGEND-A trial suggested glibenclamide (at a dose of 0.3mg/day) could change plasma glucagon levels in participants with type 2 diabetes by 30% (magnitude of effect), while the DEPTH trial suggested that participants with type 1 diabetes who experienced exercise-induced hypoglycaemia had mean plasma glucagon values of 5.54pmol/L (SD 2.14pmol/L) at the time of hypoglycaemia (defined as <3.3mmol/L).

For the non-diabetic control group, data from a clinical study in healthy volunteers [5], which used similar methodology and a plasma glucagon assay comparable to the one we will use in our trial, demonstrated that the mean plasma glucagon values during the hypoglycaemia plateau of 23.3 pmol/L (SD 5.7pmol/L).

These figures indicate that 20 participants with T1D, and 10 participants without diabetes (including 5% dropout) would give the LEGEND-D trial 80% power to detect a 30% increase in plasma glucagon levels (the primary endpoint) during induced hypoglycaemia (hyperinsulinaemic-hypoglycaemic clamp).

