## 2.2 Exploratory Endpoints

### 2.2.1 Definitions and Derivation of Exploratory Endpoints

Exploratory efficacy endpoints are defined as the difference between measurements (defined below) at baseline and at post treatment period (i.e. 0, 15, 30 and 40min):

- Plasma glucagon level is the concentration of plasma glucagon measured in pmol/L.
- Plasma somatostatin level is the concentration of plasma somatostatin measured in pmol/L.
- Blood glucose value is the concentration of blood glucose measured in mmol/L.
- Plasma C-peptide level is the concentration of plasma C-peptide measured in pmol/L.

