## 5.4 Exploratory endpoint analyses

### 5.4.1 Analysis of exploratory endpoints

1. To compare the concentration of plasma glucagon measured in pmol/L during induced hypoglycaemia (at 0, 15, 30 and 40min) in people with T1D prior to glibenclamide treatment, and at each dose step (at 0.3mg, 0.6mg and 3mg), to that of participants without diabetes (non-DM group).

A mixed-effects model (treatment x time-point) will be used to compare plasma glucagon values at each time-point (0, 15, 30 and 40min) during the hypoglycaemic phase of the hyperinsulinaemic hypoglycaemic clamp at baseline (T1D and non-DM group) and at each dose step (T1D group only).

Post-hoc analysis will be performed which will allow pairwise comparisons between the plasma glucagon values obtained at each time-point (T1D and non-DM group, see **Table 3**).

2. To compare the proportion of change in plasma glucagon concentration from euglycaemia to hypoglycaemia at each time point (0, 15, 30 and 40min) in T1D participants prior to treatment, and at each dose step (at 0.3mg, 0.6mg and 3mg) of glibenclamide, to that of participants without diabetes (non-DM group).

We will calculate the proportion of increase in plasma glucagon at each time point by taking plasma glucagon values at each time-point (0, 15, 30 and 40min) during the hypoglycaemic phase of the hyperinsulinaemic hypoglycaemic clamp divided by the value at the corresponding time-point during the euglycaemic phase.

A mixed-effects model (treatment x time-point) will be used to compare the proportion increase in plasma glucagon as dependent variable (i.e. plasma glucagon concentration during the hypoglycaemic phase vs plasma glucagon concentration during the euglycaemic phase) at each time-point (0, 15, 30 and 40min) as independent variable at baseline (T1D and non-DM group) and at each dose step (T1D group only).

Post-hoc analysis will be performed which will allow pairwise comparisons between the plasma glucagon values obtained at each time-point (see **Table 3**).

3. To compare the percentage of time spent in hypoglycaemia

**Table 1** (<4.0mmol/L of blood glucose) at each dose step (at 0.3mg, 0.6mg and 3mg) of glibenclamide, compared to baseline (T1D group only). Three separate paired t-tests will be used to compare 0mg vs 0.3mg, 0mg vs 0.6mg and 0mg vs 3mg. If the assumptions of t-test are not satisfied, then the percentages will be treated as proportion and a 2 proportions test will be used.

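### The exploratory T1D-versus-control hormone models make no provision for unequal variances and use raw quotients; a default fit would give too-narrow intervals for raw glucagon.

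*SAP*

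**What the plan says.** Section 6.2 of the SAP: "No data transformations have been identified in this SAP".

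Section 5.4.1, item 1, compares raw glucagon (pmol/L) at four time-points between the non-DM group and the T1D group, before treatment and at each glibenclamide dose, in a mixed model of treatment by time. Item 2 does the same for a quotient: the hypoglycaemic value "divided by the value at the corresponding time-point during the euglycaemic phase". Items 4 and 5 repeat the quotient for dapagliflozin, for glucagon and for somatostatin. Table 3 lists four T1D-versus-control contrasts, one for each T1D condition.

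For none of these models does the SAP state a residual or random-effect variance structure, an assumption check or a fallback. The one t-test fallback in section 5.4.1 is for percentage of time in hypoglycaemia (item 3).

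Section 1.3.4 gives the only spread figures. T1D participants "who experienced exercise-induced hypoglycaemia had mean plasma glucagon values of 5.54pmol/L (SD 2.14pmol/L"); for healthy volunteers a separate clamp study gave "mean plasma glucagon values during the hypoglycaemia plateau of 23.3 pmol/L (SD 5.7pmol/L"). The planned numbers are "20 participants with T1D, and 10 participants without diabetes (including 5% dropout").

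**The concern.** The two planning SDs differ by a factor of 2.7, and the larger one belongs to the smaller group. That is the unfavourable combination for a model with a single variance: the pooled estimate is dominated by the less variable T1D group, so the uncertainty of the control mean is understated. Common variance is the usual software default, and the SAP does not rule it out.

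The quotient raises a separate matter. The arithmetic mean of a ratio of two noisy measurements exceeds 1 even when nothing changes, and the excess depends on the coefficient of variation (CV). If the CVs of T1D participants and controls differ, the raw quotient contains a built-in group difference in the very comparison it is meant to make.

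At stake are the width of the exploratory T1D-versus-control intervals, the reading of the smaller contrasts, and the ratio comparisons with controls.

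**Working it through.** **The plan's own figure.** The SAP gives no precision figure for the control comparison. Its 80% power claim concerns a 30% rise in glucagon (0.30 × 5.54 = 1.662 pmol/L). For a two-sided paired t-test in T1D it is reached with 19 evaluable participants (power 80.2%) if the within-person correlation is about 0.35. The SAP states no correlation, so the claim can be neither confirmed nor refuted, and it does not bear on the point here.

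**Inputs (section 1.3.4).** T1D: n = 20, mean 5.54, SD 2.14. Non-DM: n = 10, mean 23.3, SD 5.7.

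**1. Variance ratio.** (5.7/2.14)² = 7.1.

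**2. Standard error at one time-point, T1D baseline versus control.**
- Common variance: (19 × 2.14² + 9 × 5.7²)/28 = 13.55, so SD 3.68 and SE = √[13.55 × (1/20 + 1/10)] = 1.43. The 95% half-width is 2.92 pmol/L (28 df).
- Group-specific: SE = √(2.14²/20 + 5.7²/10) = √(0.229 + 3.249) = 1.86. With Welch df of 10.3 the half-width is 4.14 pmol/L.
- 1.426/1.865 = 0.76, so the common-variance SE is 24% too small; 2.92/4.14 = 0.71, so the interval is 29% too narrow.

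**3. Coverage.** In 200,000 simulated normal datasets with these means and SDs, the nominal 95% common-variance interval covered 86.3% and the Welch interval 94.9%.

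**4. Closer to the planned model.** Pooling the T1D variance over four conditions gives (76 × 2.14² + 9 × 5.7²)/85 = 7.53, SD 2.74 and SE 1.06, which is 43% too small. A small simulation (250 runs per setting) of a random-intercept model with common variances, four T1D conditions and four time-points gave coverage of about 73-84% for within-person correlations of 0.3 to 0.7. It assumes equal SDs over conditions and times, and is indicative only.

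**5. Effect on the baseline conclusion.** The planning difference is 23.3 − 5.54 = 17.76 pmol/L, and 17.76/1.865 = 9.5 correct standard errors.

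**6. Log scale.** With σ² = ln(1 + CV²) and CVs of 0.386 (T1D) and 0.245 (non-DM), the log SDs are 0.37 and 0.24. The imbalance falls to 1.55-fold and reverses; it does not vanish. A common-variance interval would then cover 97.4%.

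**7. Raw quotient under no change.** For lognormal values with the same distribution in both phases and within-person correlation r, the mean of X/Y is exp[σ²(1 − r)]. Here σ² is 0.139 (T1D) and 0.058 (non-DM).

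| r (assumed) | T1D | Non-DM |
|---|---|---|
| 0 | 1.15 | 1.06 |
| 0.5 | 1.07 | 1.03 |
| 0.8 | 1.03 | 1.01 |

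This applies the hypoglycaemic CVs to the euglycaemic phase as well, for which the SAP gives no data. The geometric-mean ratio is 1 in every row.

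**The case against.** The strongest reply is that the SAP nowhere specifies a common variance. That stands: the structure is left open, and the narrow intervals follow only if the default is used. A reader might infer that the planned intervals are too narrow as written; the text does not support that.

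The evidence on spread is also thin. The two SDs come from external studies in different settings, exercise-induced hypoglycaemia in T1D and a clamp plateau in healthy volunteers. This stands too, although they are the figures the plan itself uses.

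A reader might turn the 86% coverage into a type I error of about 14%. That requires equal means with unequal SDs, a null far from the planning means and at odds with any idea that the SD rises with the mean. The coverage of the interval is the safer statement.

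A reader might also extend the point to all hormone analyses. The primary analysis (section 5.3.1) is within T1D, so the between-group SD difference does not enter it. For somatostatin and the quotients no SD is given, so narrow intervals are not shown there.

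On the quotient, items 2, 4 and 5 compare conditions and groups and do not test against 1. A bias that is equal across T1D conditions would cancel in the dose and dapagliflozin contrasts, and it shrinks as r rises. What remains is the comparison with controls, where the bias need not be equal.

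It is tempting to add that matching time-points across the two phases is meaningless. The SAP gives no rationale for the pairing, but nothing in it shows this. It is also tempting to read section 2.2.1 ("Exploratory efficacy endpoints are defined as the difference between measurements (defined below) at baseline and at post treatment period") as contradicting the quotient. That difference runs from baseline to post-treatment, while the quotient runs between phases of one clamp; the loose wording is a separate drafting matter.

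**Conclusion.** The point holds as a cheap improvement to the exploratory T1D-versus-control analyses. On the plan's glucagon SDs, a default common-variance fit would understate the standard error at one time-point by 24% (1.43 against 1.86), with about 86% coverage of a nominal 95% interval. This assumes normal data, 20 and 10 participants, and that the external SDs carry over to this trial's clamps. The baseline glucagon conclusion would not change; the harm is to interval width and to smaller contrasts.

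Separately, the raw mean quotient is biased upward under no change, and by a different amount in each group: illustratively 1.03-1.15 in T1D and 1.01-1.06 in controls. That rests on lognormality, equal CVs in both phases and an assumed correlation between 0.8 and 0.

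**What to change.** In section 5.4.1, for every exploratory hormone model that includes controls, specify group-specific variances for T1D and non-DM, at both the between-person and the residual level, with Kenward-Roger or Satterthwaite degrees of freedom. Separate residual variances alone would leave a shared between-person variance, and the quoted SDs describe spread between people.

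For items 2, 4 and 5, analyse the log of the hypoglycaemic-to-euglycaemic ratio and report geometric-mean ratios with 95% CI. Amend section 6.2 accordingly. Logging does not replace the group-specific variances, since the log SDs still differ (0.37 against 0.24).

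Optionally, use the mean of the four euglycaemic samples of the clamp as the denominator. With independent sample errors this lowers the noise variance of the log ratio from 2 to about 1.25 units, a gain of up to 37.5%.

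The cost is a SAP amendment before database lock, a few extra variance parameters, and a stated rule for values below the assay limit. No new data are needed.

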## 8 Appendices

### 8.1 Appendix 1: Reporting Conventions

**Table 3 : Groups for comparison by oral glibenclamide dose in milligrams (mg)**

|     |     | non-DM | T1D |     |     |
|-----|-----|--------|-----|-----|-----|
|     |     | 0      | 0.3 | 0.6 | 3   |
| T1D | 0   | vs.    | vs. | vs. | vs. |
|     | 0.3 | vs.    | -   | vs. | vs. |
|     | 0.6 | vs.    | -   | -   | vs. |
|     | 3   | vs.    | -   | -   | -   |

**Table 4 : Assessment of hypoglycaemia symptoms**

| Autonomic      | Neuroglycopenic          | Non-specific              |
|----------------|--------------------------|---------------------------|
| Sweating       | Inability to concentrate | Tingling around the mouth |
| Trembling      | Confusion                | Dry mouth                 |
| Flushing       | Tiredness                | Blurred vision            |
| Anxiety        | Feeling tearful          | Headache                  |
| Pounding heart | Difficulty in speaking   | Nausea                    |
| Hunger         | Odd behaviour            |                           |
|                | Incoordination           |                           |
|                | Weakness                 |                           |
|                | Drowsiness               |                           |

## 8.2 Appendix 3: Templates for Tables, Listings and Figures

**Table 5 : Baseline characteristics**

| Variable                                  | All        | T1D        | Non-DM     |
|-------------------------------------------|------------|------------|------------|
| Age in years:                             |            |            |            |
| Mean (SD)                                 | xx (xx)    | xx (xx)    | xx (xx)    |
| Median (Q1-Q3)                            | xx (xx-xx) | xx (xx-xx) | xx (xx-xx) |
| Gender: N (%)                             |            |            |            |
| Male                                      | xx (xx.xx) | xx (xx.xx) | xx (xx.xx) |
| Female                                    | xx (xx.xx) | xx (xx.xx) | xx (xx.xx) |
| BMI (kg/m  ):                 |            |            |            |
| Mean (SD)                                 | xx (xx)    | xx (xx)    | xx (xx)    |
| Median (Q1-Q3)                            | xx (xx-xx) | xx (xx-xx) | xx (xx-xx) |
| SBP(mmHg):                                |            |            |            |
| Mean (SD)                                 | xx (xx)    | xx (xx)    | xx (xx)    |
| Median (Q1-Q3)                            | xx (xx-xx) | xx (xx-xx) | xx (xx-xx) |
| DBP (mmHg):                               |            |            |            |
| Mean (SD)                                 | xx (xx)    | xx (xx)    | xx (xx)    |
| Median (Q1-Q3)                            | xx (xx-xx) | xx (xx-xx) | xx (xx-xx) |
| Resting Heart rate
(beats per minute): |            |            |            |
| Mean (SD)                                 | xx (xx)    | xx (xx)    | xx (xx)    |
| Median (Q1-Q3)                            | xx (xx-xx) | xx (xx-xx) | xx (xx-xx) |
| Blood Glucose (mmol/L):                   |            |            |            |
| Mean (SD)                                 | xx (xx)    | xx (xx)    | xx (xx)    |
| Median (Q1-Q3)                            | xx (xx-xx) | xx (xx-xx) | xx (xx-xx) |

|                                |            |            |            |
|--------------------------------|------------|------------|------------|
| Plasma Glucagon (pmol/L):      |            |            |            |
| Mean (SD)                      | xx (xx)    | xx (xx)    | xx (xx)    |
| Median (Q1-Q3)                 | xx (xx-xx) | xx (xx-xx) | xx (xx-xx) |
| Plasma C-peptide (pmol/L):     |            |            |            |
| Mean (SD)                      | xx (xx)    | xx (xx)    | xx (xx)    |
| Median (Q1-Q3)                 | xx (xx-xx) | xx (xx-xx) | xx (xx-xx) |
| Plasma Somatostatin (pmol/L):  |            |            |            |
| Mean (SD)                      | xx (xx)    | xx (xx)    | xx (xx)    |
| Median (Q1-Q3)                 | xx (xx-xx) | xx (xx-xx) | xx (xx-xx) |
| Blood: HbA1c, FBC*, U&E, LFTs. |            |            |            |
| Mean (SD)                      | xx (xx)    | xx (xx)    | xx (xx)    |
| Median (Q1-Q3)                 | xx (xx-xx) | xx (xx-xx) | xx (xx-xx) |

\*Haemoglobin, white cell count, haematocrit and platelets

## 9 Document history

| Version Number | Effective Date | Significant Changes                           |
|----------------|----------------|-----------------------------------------------|
| 0.1            | 2023-09-19     | Initial version                               |
| 0.2            | 2024-06-17     | Second draft following review by RLC, AIA     |
| 0.3            | 2024-07-11     | Third draft following review by RLC, AIA      |
| 0.4            | 2024-10-17     | Fourth draft following review by RLC, AIA, IS |
| 1.0            | 2024-11-21     | Final version                                 |

RLC-[name], AIA-[name], IS- [name]

[figure not shown]

This Document has been Signed with a **secure electronic signature** via E-Sign.

